# Randomised, double-blind, placebo controlled multi-centre study to assess the efficacy, tolerability and safety of Enterosgel® in the treatment of irritable bowel syndrome with diarrhoea (IBS-D) in adults

**DOI:** 10.1186/s13063-020-4069-x

**Published:** 2020-01-30

**Keywords:** Clinical trial, Diarrhoea, Enterosgel, Intestinal adsorbent, Irritable bowel syndrome, Medical device, Placebo-controlled, Randomised controlled trial

## Abstract

**Background:**

Irritable bowel syndrome (IBS) with diarrhoea (IBS-D) is a common and chronic condition that can significantly impair quality of life. The emergence of new drugs for IBS-D has been slow and there is a need for new treatments, including drug-free treatments, which are easy to use and suitable for different patient groups. Currently available drug-free treatments include Enterosgel®, an intestinal adsorbent approved for use in IBS-D and acute diarrhoea and available over-the-counter in the UK and 30 countries worldwide. The aim of this randomised, double-blind, placebo-controlled, multi-centre study is to test the efficacy and safety of Enterosgel® compared to placebo in symptomatic treatment in IBS-D.

**Methods/design:**

We will recruit 430 participants with IBS-D from approximately 30 primary and secondary care sites in England. Participants meeting the required abdominal pain and stool consistency criteria over a 2-week screening period will be randomly allocated to receive blinded treatment (Enterosgel® or placebo) for 8 weeks. This will be followed by an 8-week open-label treatment phase with Enterosgel®. Participants will be allowed to adjust their daily dosage during both phases based on their symptoms. Participants will then return to standard care and those who responded to treatment will receive a follow-up call 8 weeks later. Co-medication with loperamide will be permitted and use recorded. The primary outcome measure is the percentage of participants defined as responders for abdominal pain and stool consistency during at least 4 weeks in the 8-week blinded phase. Secondary outcome measures include stool frequency, stool consistency, abdominal pain, bloating, urgency, adequate relief, questionnaire scores and rescue medication use. Exploratory outcomes will be assessed in subsets of participants including qualitative and quantitative data on faecal microorganisms and biomarkers and gut-related measurements from magnetic resonance imaging data.

**Discussion:**

This is the first large scale randomised controlled trial investigating Enterosgel® in IBS-D. A study design with blinded phase followed by an open-label phase was chosen to encourage participation and study completion. Demonstrating that Enterosgel® is effective and safe in IBS-D could encourage adoption by patients and healthcare professionals and foster future clinical trials assessing its use in related conditions.

**Trial registration:**

ISRCTN17149988. Prospectively registered on 14 November 2017.

## Background

Irritable bowel syndrome (IBS) is a common chronic functional bowel condition characterised by symptoms of abdominal pain and/or discomfort associated with altered bowel habits, in the absence of a structural or organic cause [1, 2]. The Rome IV criteria provide the latest diagnostic criteria for IBS [3] and its three main subtypes, i.e. IBS with diarrhoea (IBS-D), IBS with constipation (IBS-C) and mixed IBS (IBS-M). The specific cause of the disorder is not fully understood [4, 5], but among other factors may include genetic disposition, gut immune dysfunction, immune activation, gut dysbiosis, infective and dietary triggers and changes to gut permeability [6–8].

IBS is common worldwide, with an estimated prevalence globally of 11.2% [9, 10], although a more recent study based on the Rome IV criteria for diagnosis suggests a reduced estimate of around 5.0% [11]. In the UK, the prevalence is estimated to be between 10% and 20% [12]. It occurs in all age groups, including children and the elderly, although it predominantly affects adults of working age. Internationally, the overall prevalence of IBS in women is 67% higher than in men, although there are differences in the sex-specific prevalence between geographic regions [9]. The prevalence of each subtype can vary depending on the classification used. According to the World Gastroenterology Organisation, up to one-third of cases are IBS-D, up to one-third of cases are IBS-C and IBS-M accounts for up to one-third to one-half of cases [13].

IBS imposes a substantial burden on society, impacting on patients’ quality of life, work productivity and social activities, as well as on direct and indirect healthcare costs. In the UK, direct healthcare costs include an estimated eight to ten general practice (GP) visits per year [14] and associated visits for the 29% of IBS patients who are referred to secondary care specialists before returning to primary care for their long-term management [15]. Overall healthcare costs for IBS are comparable to those of other chronic diseases with a similar prevalence, such as congestive heart failure, hypertension, asthma and migraine [16].

IBS is a challenging condition to treat mainly as a result of its complex multi-factorial nature. Currently, no single universally effective approach is available for the management of IBS [13], but lifestyle or dietary changes are often implemented as the first step of management. For example, the low Fermentable, Oligo-, Di-, Mono-saccharides and Polyols (FODMAP) diet can help symptoms [12] but can be difficult to implement without support from a dietician. Probiotic use is also becoming more common and has shown to improve symptoms in patients with IBS-D [17]. Potential treatment targets include mediators such as histamine and serotonin, which are postulated to play a causative role in IBS, and bacterial products and bile acids, which also have been implicated in the generation of IBS symptoms [7, 8]. Medications for treating IBS-related symptoms include antispasmodics, psychotropic agents, bulking agents and 5-HT receptor antagonists. However, many of these drugs have proven to be inadequate for the relief of symptoms and some have safety issues [18]. Less than one-third of patients with IBS are satisfied with their current therapy, with only 45% describing their prescription drugs as “effective” [19]. Minimal understanding of the pathophysiological aspects of the condition, poorly designed studies providing unconvincing evidence, inconsistent literature on IBS treatments and high placebo response rates (30–80%) in short term studies [20–22] are all likely to contribute to the lack of effective treatments. There is, therefore, a need for well-designed clinical trials on new therapies for IBS-D.

Previous clinical studies on intestinal adsorbents have shown some improvement in the symptoms of IBS-D, but are likely to have been underpowered for many important outcome measures [23, 24]. The rationale for the use of intestinal adsorbents in the management of IBS symptoms is their ability to bind to various mediators and toxins and remove them from the gastrointestinal tract in the stools. There is also evidence from research on the intestinal adsorbent dioctahedral smectite for enhancement of the intestinal barrier function, which counteracts disruption from pro-inflammatory cytokines [25, 26]. One of the intestinal adsorbents approved for use in IBS-D and available over-the-counter in the UK is Enterosgel®, which is a drug-free treatment developed for binding toxins and other harmful substances in the gastrointestinal tract [27]. It is suitable for different patient groups, including children and the elderly. Although there has been extensive research on Enterosgel®, including two pilot studies in IBS-D reporting a normalisation of stool frequency and form and decrease in bodily pain [28, 29], and a UK based study in acute diarrhoea [30], so far none of the conducted studies have included a placebo control arm. The difficulty has been that gel-like substances with a consistency similar to commercially available Enterosgel® (for example gelatin or starch based) could potentially have effects in the gastrointestinal tract and their suitability for use as a placebo would require validation. This randomised, double-blind, placebo-controlled, multi-centre study will use an innovative approach to overcome this challenge. The aim is to test the efficacy and safety of Enterosgel® over placebo in symptomatic treatment in 430 adults with IBS-D diagnosed according to the Rome IV criteria.

## Methods/design

### Study design

This will be a multi-centre, parallel arm, randomised, double-blind, placebo-controlled trial to evaluate the efficacy, tolerability and safety of a medical device, Enterosgel®, in the treatment of IBS-D in adults (Fig. 1). The study involves a 2-week screening phase, after which eligible participants are randomised to blinded treatment (Enterosgel® or placebo) for 8 weeks. Following the double-blind treatment phase, all participants will receive open-label Enterosgel® treatment for a further 8 weeks. At the end of the open-label treatment phase, all participants will return to standard care; however, those who responded to open-label treatment will receive a follow-up call 8 weeks later.

**Fig. 1 Fig1:**
[figure not shown]
Study design

The study will involve four study visits and one to two follow-up calls: screening visit (− 2 weeks), baseline visit (0 weeks), follow-up call (2 weeks), follow-up visits at weeks 8 and 16 and a follow-up call at week 24 (only for participants who responded to open-label treatment).

### Eligibility criteria

#### Inclusion criteria

At screening visit, the following criteria must be met:
Written informed consentIrritable bowel syndrome with diarrhoea (IBS-D) according to Rome IV criteria [3]Aged 16–75 yearsConsidered suitable to take part in the study by the consenting investigator

At baseline visit, before starting the intervention, the following additional criteria must be met:
Diary completed on at least 11 of 14 days (≥ 75%) during the screening period

#### Exclusion criteria

At screening visit, the participant will not be eligible to proceed if they meet any of the following criteria:
Previously diagnosed coeliac disease (must be confirmed from medical records before randomisation)Previously diagnosed IBD (must be confirmed from medical records before randomisation)Previous bowel cancer or bowel resection (must be confirmed from medical records before randomisation)Other previously known gastrointestinal disorder contributing to the diarrhoea according to principal investigator’s or sub-principal investigator’s evaluation (must be confirmed from medical records before randomisation)Unexplained weight lossUnexplained rectal bleeding (not including a short history of typical haemorrhoidal bleeding in patients aged < 45 years)Previous use of Enterosgel®Use of antidepressant agents, unless used at a stable dose for at least 6 weeksUse of any probiotic supplements, other intestinal adsorbents (activated charcoal, kaoline, diosmectite), slow-release medications or strong opioids (World Health Organisation Step III) (must be confirmed from medical records before randomisation)Participation in any research where treatment is provided, or was provided in the last 3 monthsPregnancy or not willing to use contraception for the duration of the study screening and treatment periods

At baseline visit, the participant will not be eligible to proceed to randomisation if they no longer meet one or more of the criteria above, or if they demonstrated:
Loose stools (Bristol Stool Form Scale (BSFS) 6 or 7) on less than 3 days during the 14 days after screening visit, and/orAverage abdominal pain < 3 during the 14 days after screening visit (scale 0–10: 0 = no pain; 10 = worst possible pain).

### Interventions

#### Experimental intervention

The commercially available Enterosgel® product contains 30% water and 70% polymethylsiloxane polyhydrate (PMS-PH), which is a three-dimensional crosslinked polymer of methylsiliconic acid formed by polycondensation in which hydroxyl groups form stable siloxane bonds. Since over-the-counter Enterosgel® is instructed to be taken by diluting 1–1.5 tablespoons of the product in 100–200 ml water, a water-based placebo offers an alternative to a gel-like placebo. In order to enable a water-based placebo to be used as a comparator in this trial, the blinded Enterosgel® will be provided in a pre-diluted form in 90-ml tubes containing 15 g Enterosgel® in 67.5 ml potable water. The placebo will be provided in the same 90-ml tubes, each containing a single dose of treatment. Study-specific dosage instructions for the double-blind treatment period allow participants to adjust their daily dosage based on their symptoms (Additional file 1).

For the open-label treatment phase, all participants will receive Enterosgel® in standard 15-g sachets, which are identical to those available over-the-counter in the UK. Study-specific dosage instructions also allow participants to adjust their daily dosage based on their symptoms (Additional file 2).

#### Packaging, labelling and supply

Both the placebo and Enterosgel® dilutions for double-blind treatment phase are manufactured in accordance with Good Manufacturing Practice (GMP) by Bioline Products s.r.o. (CZ), packed into identical 90-ml tubes and labelled in accordance with Annex I of the European Council Directive 93/42/EEC concerning Medical Devices. All study treatment will be stored at a Medicines and Healthcare products Regulatory Agency (MHRA)-approved warehouse facility (Wasdell Group, UK). After each randomisation, the site research team will email a request form with a unique randomisation code to a dedicated email address, which can only be accessed by Sponsor’s (Enteromed Ltd, UK) unblinded study coordinators. A coordinator will check the randomisation code against a pre-generated randomisation code list to determine whether it corresponds to placebo or Enterosgel® and will then submit a shipment request to the warehouse through a secure online portal. Supplies will be dispatched for delivery directly to the study participants within two calendar days from receiving the request (next day delivery for orders submitted before 2 pm). The supplied treatment will be sufficient to cover the entire 8-week treatment phase even if the maximum dose is taken every day.

Open-label treatment will be provided in sachets containing 15 g Enterosgel® and labelled in accordance with regulatory requirements. After a participant has been entered into the open-label phase, the site research team will send a treatment request to the Sponsor who will submit a shipment request to the warehouse as described above.

Treatment use and compliance are monitored through the daily study diary where the patients are asked to record how many doses of study treatment they used each day. If they did not take any treatment on a given day, then the electronic diary would also ask to provide a reason. These data are monitored by the study team on a weekly basis and the site teams are contacted if any issues are identified. Participants are not required to return any empty or unused tubes or sachets. Should the participant run out of study treatment during the study, they can request additional supplies through their research site.

#### Concomitant interventions

Participants will be allowed to continue to take antidepressant agents at a stable dose, provided that they had been taking a stable dose for at least 6 weeks before providing written informed consent.

Use of probiotic supplements, other intestinal adsorbents (activated charcoal, kaoline, diosmectite), slow-release medications or strong opioids will not be permitted during the study. To minimise the risk that Enterosgel® could adsorb concomitant medications in the gut, it will be recommended to leave at least 2 hours before and after taking the study treatment and taking any oral medications.

Loperamide will be provided to all study participants for use as a rescue medication during the double-blind and open-label treatment phases. Participants will be advised not to make any significant changes to their diet during the trial.

### Outcome measures

#### Primary outcome measure

The primary outcome measure is the percentage of participants defined as responders for abdominal pain *and* stool consistency during at least 4 weeks in the 8-week treatment period, where:
An “abdominal pain intensity weekly responder” is defined as a participant who experiences a decrease in the weekly average abdominal pain score of at least 30% compared with baseline. The weekly average abdominal pain score is derived by scoring the worst pain experienced each day and taking the average for 1 week.ANDA “stool consistency weekly responder” is defined as a participant who experiences a 50% or greater reduction in the number of days per week with at least one stool that has a consistency of BSFS type 6 or 7 compared with baseline.

A participant needs to be a responder for both abdominal pain and stool consistency in the same week to be considered a responder that week.

#### Secondary outcome measures

Secondary outcome measures for the double-blind treatment phase and open-label treatment phase are:
Stool frequency (mean over 8 weeks and the last 4 weeks based on a daily question in the study diary).Stool consistency assessed as average number of days/week with Bristol Stool Scale type > 5 (mean over 8 weeks and the last 4 weeks based on a daily question in study diary, and percentage of responders where responder is defined as a participant with ≥ 50% reduction in this outcome compared with baseline (i.e. screening period)).Abdominal pain (mean over 8 weeks and the last 4 weeks based on a daily question in the study diary, and percentage of responders where responder is defined as a participant with ≥ 30% reduction in abdominal score compared with baseline (i.e. screening period)). Abdominal pain is scored on a scale from 0 to 10, where 0 means no pain at all and 10 means the worst possible pain imaginable.Bloating (mean weekly score over 8 weeks and the last 4 weeks based on a weekly question in study diary). Scale of bloating is from 0 to 6, where 0 means bloating was not bothersome at all and 6 means bloating was greatly bothersome.Urgency (mean weekly score over 8 weeks and the last 4 weeks based on a weekly question in the study diary). Scale of urgency is from 0 to 6, where 0 means no urgency at all and 6 means a very great deal of urgency with bowel movements.Adequate relief of global IBS symptoms (percentage of participants based on a weekly question in study diary).IBS Severity Scoring System (IBS-SSS) score (weekly questionnaire)IBS-related Work Productivity and Activity Impairment (WPAI:IBS; weekly questionnaire to assess percentage work time missed due to IBS, percentage impairment while working due to IBS, percentage overall work impairment due to IBS, percentage activity impairment due to IBS).IBS Quality of Life (IBS-QOL) score (4-weekly questionnaire)Patient Health Questionnaire 12 Somatic Symptom (PHQ-12 SS) scale (4-weekly questionnaire to assess total score and individual symptoms headache (e.), tiredness (n.) and sleep (o.))Use of rescue medication, i.e. loperamide (total number of days loperamide used each week and average over 8 weeks based on a weekly question in study diary)Adverse events (percentage of participants reporting serious adverse event (SAE) and adverse events (AE) possibly related to treatment and total number of SAEs and AEs reported)

Data for secondary outcome measures for the follow-up phase will be collected at week 24 follow-up call using an investigator questionnaire developed specifically for this study. Data will only be collected from participants who reported adequate relief in the last 4 weeks of the open-label treatment phase. The outcomes for the follow-up phase are:
Maintenance of treatment benefit (percentage of participants who report increased or maintained treatment benefit at 8 weeks)Enterosgel® use (percentage of participants who report having used Enterosgel® during the follow-up period; frequency of use in these participants)Loperamide use (percentage of participants who report having used less loperamide during the follow-up period than before the trial)

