#### Planned analyses

Analyses will be conducted following intention-to-treat (ITT) principles with outcomes analysed according to the participant’s original, randomised group irrespective of deviations based on non-compliance. The statistician will remain blind to allocation until after the trial is complete and data locked.

All participant baseline data will be summarised descriptively by trial arm. Continuous measures will be reported as means and standard deviations while the categorical data will be reported as counts and percentages.

The primary outcome measure is the percentage of participants defined as study period responders. Where necessary, multiple imputation will be used to impute missing daily abdominal pain and stool consistency scores before the required derived variables are generated (see “Missing data” section below for further details). Once obtained, the primary outcome data will be summarised descriptively and logistic regression will be used to compare the placebo and Enterosgel® groups, with odds ratio and 95% confidence interval reported.

Secondary outcome data will be summarised descriptively at different time points by trial arm. The secondary outcomes will be analysed using either analysis of covariance (ANCOVA) models (for stool consistency and abdominal pain following multiple imputation), linear mixed effects models (continuous secondary outcomes), or mixed effects logistic regression models (binary secondary outcomes). The mixed effects models will contain indicator variables for treatment group and, where appropriate, time plus a time-treatment interaction. The models will be adjusted for the baseline measure of the outcome, where available.

Significance tests will be two-sided at the 5% significance levels unless otherwise stated. All models in the analysis of the double-blind and open-label phases will be adjusted for participant’s age and gender at baseline. Analyses will be undertaken in Stata v13 or later (to be confirmed in the final report).

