#### Safety assessments

Types of AEs associated with medical devices and applicable for this study are defined in accordance with the European Commission guidelines on medical devices [34]. AEs will be collected throughout the study from screening visit until week 24. The following information will be recorded for all AEs: medical term of the AE (SNOMED CT terminology), start date and date of resolution, seriousness, severity, study treatment action, outcome, relationship with the study treatment and expectedness. In case of a SAE related to study treatment(s) or procedures, the participant should be withdrawn from the study. Expectedness will be determined based on known side effects listed on the latest Instructions for Use for Enterosgel®. Currently listed known side effects of Enterosgel® are nausea and constipation.

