#### Reporting of serious adverse events and other safety-related events

The sponsor must report all SAEs, whether initially considered to be device-related or not, immediately to the MHRA. The Research Ethics Committee should be notified of any related and unexpected SAEs within 15 days. Reports of related and unexpected SAEs in double-blind trials should be unblinded. However, local investigators should only receive information on the code-break if it is necessary for the safety of the participant.

AEs suspected to be related only to an authorised auxiliary medicinal product (i.e. loperamide), and not resulting from a possible interaction with the investigational treatment, should be reported through the Yellow Card Scheme.

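### The participant-level percentage for non-serious adverse events counts only those judged possibly related to treatment; all-cause events appear only as an event total

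*Protocol article*

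**What the plan says.** Under Secondary outcome measures, the last item in the list for the double-blind and open-label phases defines the adverse event outcome in two parts:

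- At participant level: "percentage of participants reporting serious adverse event (SAE) and adverse events (AE) possibly related to treatment".
- At event level, with no relatedness condition: "total number of SAEs and AEs reported".

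Safety assessments states that "AEs will be collected throughout the study from screening visit until week 24". The items recorded for every event include seriousness, severity and "outcome, relationship with the study treatment and expectedness". The same section adds: "Currently listed known side effects of Enterosgel® are nausea and constipation".

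Planned analyses states: "Secondary outcome data will be summarised descriptively at different time points by trial arm". No formal test of adverse event percentages is described. Under Blinding, participants and research teams do not know the allocation.

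**The concern.** The title of the trial names tolerability and safety beside efficacy, and the Background says that none of the product's earlier studies had a placebo arm. A placebo arm lets harms be compared by allocation alone, with no one having to decide what caused each event. The participant-level outcome brings that decision back for non-serious events, because an event enters the percentage only if someone judged it possibly related.

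An effect that is real but not recognised as such in individual cases would then be missing, wholly or partly, from the percentage by arm. The event total would still contain it, but in a form that mixes how many people were affected with how often each of them reported. What is at stake is how informative the headline safety percentage is. The primary analysis is untouched and no data are lost.

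**Working it through.** **1. What the definition admits.** The position of the words on relatedness leaves two readings.

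| Reading | SAE percentage | Non-serious AE percentage |
|---|---|---|
| The limit applies to AEs only | any cause | possibly related only |
| The limit applies to SAEs and AEs | possibly related only | possibly related only |

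On both readings the non-serious percentage is filtered. On the second, the SAE percentage is filtered too. No all-cause participant percentage for AEs is named anywhere in the article.

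**2. Whether the event total fills the gap.** It is unfiltered and, under Planned analyses, would be shown by arm. It does not give the number of participants affected. Ten participants with one event each and one participant with ten events both give a total of 10, but 10 participants and 1 participant affected.

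**3. Whether the data for an all-cause percentage exist.** Yes. Every AE is recorded together with its relationship to treatment, so both the filtered and the unfiltered percentage can be derived.

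**4. How much the filter could matter.** The document gives no AE rate, so there is no stated safety figure to reproduce. What follows is illustration on assumed rates. The only input from the document is the number per arm: 430 enrolled at 1:1 gives 430 / 2 = 215.

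Let p0 and p1 be the all-cause percentages on placebo and active, and f the share of affected participants whose events are judged possibly related, equal in both arms because attribution is blinded. The visible difference is f × (p1 − p0). The last two columns give the approximate chance that a two-sided 5% comparison with 215 per arm would pick it up. This only indicates how visible the difference is, since the plan is descriptive.

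| f | 30% v 40%: visible difference | 30% v 45%: visible difference | Chance, 30% v 40% | Chance, 30% v 45% |
|---|---|---|---|---|
| 1.00 | 10.0 | 15.0 | 59% | 90% |
| 0.75 | 7.5 | 11.3 | 42% | 74% |
| 0.50 | 5.0 | 7.5 | 28% | 51% |
| 0.25 | 2.5 | 3.8 | 15% | 27% |

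For example, f = 0.50 with 30% and 40% gives 15% and 20%. The standard error is √[(0.15 × 0.85 + 0.20 × 0.80) / 215] = 3.7 points, against a difference of 5.0.

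**5. The filter can also work the other way.** Suppose that 25% of the 30% background is attributed in each arm and all of a 10-point excess. The filtered percentages are 0.25 × 30 = 7.5% and 7.5 + 10 = 17.5%. The difference stays at 10 points with less background noise: the standard error is √[(0.075 × 0.925 + 0.175 × 0.825) / 215] = 3.2 points, against √[(0.30 × 0.70 + 0.40 × 0.60) / 215] = 4.6 unfiltered. If instead none of the excess is attributed, the filtered difference is 0. Which case applies cannot be known in advance, so both percentages are needed.

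**The case against.** **All-cause events are already an outcome.** The same list item adds an unfiltered total, and it is summarised by arm. This stands: it would be wrong to say that unattributed events are left out of the safety outcome. What remains is narrower, namely that their participant-level frequency is not named.

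**It belongs in the statistical analysis plan.** AE tables are usually laid out there, and that plan is not shown. This holds for events by medical term, confidence intervals and table layout. Separate presentation of the phases is already implied by the outcome list. It does not hold for the outcome definition, because the article itself chooses the participant-level measure and writes the relatedness condition into it. An any-AE row may well exist in the unseen plan, which limits the weight of the point.

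**Attribution is blinded.** This stands for the double-blind phase. A tendency to attribute the two listed effects more readily would act in both arms, so a reader should not infer a bias favouring one arm. Dilution remains possible. In the open-label phase everyone takes the active product and relatedness is judged with that known.

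**Adsorbed co-medication.** The text under Concomitant interventions that begins "To minimise the risk that Enterosgel® could adsorb concomitant medications in the gut" might lead a reader to infer that loss of effect of another medicine would be rated unrelated and so be missed. The document does not support that. It makes the risk explicit, recommends spacing oral medicines from the study treatment, and bars slow-release medicines. Its loperamide reporting rule covers only events "not resulting from a possible interaction with the investigational treatment", so possible interaction is at least considered there. An event that a site judged possibly related would count. Loss of effect is one possible example of an unattributed event and no more.

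**Other safeguards.** SAEs go to the regulator whatever their cause, a data monitoring committee reviews safety, and the PHQ-12 SS captures somatic symptoms without a causality filter. These help, but none gives the proportion of participants with an adverse event.

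**Conclusion.** The point holds in a limited form. As written, the participant-level percentage for non-serious AEs is confined to events judged possibly related, and the only all-cause AE measure is an event count that cannot show how many participants were affected. It is also unclear whether the condition extends to SAEs.

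The likely consequence in the double-blind phase is dilution of a true difference, not differential bias. Its size is unknown: the assumed scenarios run from no loss to complete loss of the excess, and they rest on all-cause rates and attribution shares that the document does not give. No figure in the protocol is wrong, and the data allow the all-cause percentage to be produced at any time. This is a cheap improvement to an outcome definition and does not threaten the trial's conclusions.

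**What to change.** Define the safety outcome as two percentages, compared by randomised arm in the double-blind phase: participants with at least one AE of any cause, and participants with at least one SAE of any cause. Keep the possibly related percentage and the event totals as additional rows. State that the relatedness condition does not limit SAEs.

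The cost is one or two table rows from data already recorded for every event. The downside is that all-cause percentages contain more background events. Randomisation balances these between arms in expectation, but they widen the uncertainty of the difference, which is why the related-event row should stay beside them.
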